#### ​Randomisation

The study statistician will conduct the randomisation. Each PICU will be allocated a unique ID. At study commencement, sites will be classified on size based on the number of children receiving IMV in the PICU recorded in the 2017 PICANet database. Randomisation will be balanced on cluster size such that clusters will be randomised in blocks of size 4, with each block containing two large and two small clusters.

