### Study design and setting

#### ​Setting

SANDWICH is a cluster randomised stepped wedge trial in 18 NHS PICUs. Participating PICUs provide clinical audit data to the Paediatric Intensive Care Audit Network (PICANet) database (www.picanet.org.uk). PICUs will be eligible if they agree to nominate local champions, comply with the protocolised weaning intervention and staff document a willingness to participate in training.

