## Analysis

### Clinical evaluation

Baseline characteristics will be summarised by exposure and non-exposure to the intervention using summary statistics. PICUs will be classified as being exposed to the intervention on completion of the training period. The primary aim is to evaluate whether there is a difference in the duration of hours on ventilation before and after exposure to the intervention. We will use survival analysis (time to extubation) and estimate an HR for the intervention effect. This means that higher HRs will signify success of the intervention.

We will know exact survival times (ie, times until successful extubation) for most children, but children who die on ventilation, are transferred to another unit, are not weaned before transitioning to the training phase or are not weaned by 90 days will not have a known extubation time. We will treat such events as censored observations, making the assumption that children who are censored for any of these reasons will have an extubation time (ie, were or would have been removed from ventilation) greater than the time until they died or were transferred. These are plausible assumptions. In order to minimise any potential within cluster contamination, we will censor children when their PICU moves into the transition phase. When the PICU moves into the intervention phase, only new admissions will be included.

We will explore various models, but anticipate fitting a Cox proportional hazards model, perhaps with some treatment-by-covariate interaction to incorporate any non-proportionality. Allowance will be made for clustering using a frailty term for each PICU (this is similar to a random effect in a mixed-effects model). We will also adjust for calendar time, since the intervention is sequentially rolled-out. If a child is readmitted or transferred, they will be treated as new events and acknowledged within our analysis. Our primary estimate of the treatment effect will be a cluster and time-adjusted HR along with 95% CIs. Time adjustment is essential because this is a stepped wedge trial.

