Secondary analysis will adjust for individual and cluster level covariates (such as the adherence score) and these will be prespecified. Null hypotheses and analyses for secondary outcomes take a similar form to that for the primary outcome. Where outcomes are not survival times, analysis will use the generalised linear mixed model, reporting risk differences for binary outcomes and mean differences for continuous outcomes (all adjusting for cluster and time effects).

Full details of the analyses will be given in the statistical analysis plan.

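### Site order is randomised in size-balanced blocks, but the stated primary hazard ratio adjusts only for cluster and time; adding the size stratum is a small, almost free gain in precision

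*Protocol article*

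**What the plan says.** Under Randomisation, sites are classed by volume: "sites will be classified on size based on the number of children receiving IMV in the PICU recorded in the 2017 PICANet database". The order of crossing over is then restricted: "Randomisation will be balanced on cluster size such that clusters will be randomised in blocks of size 4", and every block holds two sites of each size class.

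Under Clinical evaluation, the model is left partly open ("We will explore various models, but anticipate fitting a Cox proportional hazards model"). Clustering is handled by a random term: "Allowance will be made for clustering using a frailty term for each PICU". The adjustment set of the headline result is stated without qualification: "Our primary estimate of the treatment effect will be a cluster and time-adjusted HR along with 95% CIs". Covariates appear one step later: "Secondary analysis will adjust for individual and cluster level covariates (such as the adherence score) and these will be prespecified". Size is not named in either analysis.

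The Sample size section gives about 80% power for a 1-day difference. It treats the outcome as continuous, with SD 9.6 days, ICC 0.005 (range 0.001 to 0.01), an exchangeable correlation structure, 28 patients per four-week block and an expected total of 9520.

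**The concern.** A factor used to restrict a randomisation normally belongs in the primary model. The design has already removed part of the chance imbalance in that factor. A model that ignores it still counts the factor's variance as error, so its standard error is somewhat too large, and any precision the factor could supply is lost.

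In a stepped wedge trial one might expect this not to matter, because size is constant within a PICU and each PICU serves as its own control. That is exact with fixed PICU effects. With a random frailty the estimate also draws on comparisons between PICUs that are in different phases at the same calendar time, and there a size effect on duration of ventilation does not cancel. What is at stake is efficiency, in a trial planned at only about 80% power.

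**Working it through.** **Inputs from the protocol.** There are 18 PICUs, two of them at one site, so 17 sites are randomised (Setting, Design). Two baseline four-week periods come first, one site steps every four weeks, each site has two training periods without recruitment, and two final periods follow. The last site trains in periods 19 and 20, so there are 22 periods and each site recruits in 20. SD, difference, ICC and block size are from Sample size.

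**Assumptions.** The test is two-sided at 5%. There are four blocks of two large and two small sites, and the 17th site is large or small at random. The share R of between-PICU variance explained by size is varied from 0 to 1, because the documents do not give it.

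**Step 1: reproduce the plan.** N = 17 × 20 × 28 = 9520, which matches. The total variance is 9.6² = 92.16. The between-site variance is 0.005 × 92.16 = 0.461 (SD 0.68 day). The error variance of a site-period mean is 0.995 × 92.16 / 28 = 3.275. Generalised least squares with a random site intercept and fixed period effects gives SE 0.356 day. Power = Φ(1/0.3559 − 1.960) = Φ(0.850) = 80.2%, in line with the stated 80%.

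**Step 2: is between-PICU information used?** With fixed site effects the SE is 0.388. The within-site share of the information is (0.356/0.388)² = 0.84, so about 16% comes from between-site comparisons. Consistent with this, power depends on the ICC: 87.5% at 0.001 and 77.6% at 0.01.

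**Step 3: size left out.** The model SE stays at 0.356. Let w be the weight that the estimate gives to each site's intercept, and s = ±1 the size code. The true variance under blocked allocation is the error part plus 0.461 × [(1 − R) Σw² + R Var(Σws)], with Var(Σws) taken from 20,000 draws of the blocked order. Then type I error = 2Φ(−1.960 × 0.3559 / SE_true), and power = Φ((1 − 1.960 × 0.3559) / SE_true).

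**Step 4: size included.** The same model gains a fixed large/small term, and the between-site variance falls to 0.461 × (1 − R). Power is averaged over blocked orders.

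A share R corresponds to a large-versus-small difference in mean duration of d = 2 × 9.6 × √(0.005R) days, for equal groups.

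| R | d (days) | True SE, size out | Model SE / true SE | Type I error, size out | Power, size out | Power, size in |
|---|---|---|---|---|---|---|
| 0 | 0 | 0.356 | 1.00 | 5.0% | 80.2% | 80.1% |
| 25% | 0.68 | 0.352 | 1.01 | 4.7% | 80.5% | 81.5% |
| 50% | 0.96 | 0.348 | 1.02 | 4.5% | 80.8% | 83.5% |
| 75% | 1.18 | 0.344 | 1.04 | 4.2% | 81.1% | 86.6% |
| 100% | 1.36 | 0.339 | 1.05 | 4.0% | 81.4% | 92.0% |

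Worked row, R = 50%: size out, (1 − 0.6975)/0.3477 = 0.870, so 80.8%. Size in, SE 0.341, and 1/0.3409 − 1.960 = 0.973, so 83.5%. The gain is 2.7 points.

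**Step 5: robustness.** At R = 50% the change is about 88.0% to 89.3% for ICC 0.001, and 78.0% to 80.3% for ICC 0.01. With unequal sites (assumed 40 versus 16 per period, scaled to a mean of 28), power without size is about 79.8% and the gains are similar. Simulated trials refitted by REML (1,000 per scenario, R = 0, 0.5 and 0.9) gave type I error of 3.7% to 6.0% without size and 4.5% to 6.2% with it, in agreement within simulation error.

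**The case against.** Four objections carry weight.

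- The model is only anticipated, and details are deferred to an analysis plan that is not shown and may already include size. This stands as a caution. But the article does more than stay silent: it states the adjustment set of the primary estimate and places cluster-level covariates in the secondary analysis.
- About 84% of the information is within PICU, where size cancels. This is correct, and it is why the gains are modest at plausible values of R.
- Nothing in the document links PICU volume to duration of ventilation. This is also correct. If there is no link, adding the term costs 0.1 point of power. The larger gains need a two-level split to explain half or more of an already small between-PICU variance.
- The figures are for a linear model in days, whereas the primary analysis is expected to be a Cox frailty model. This stands too. The approximation is the protocol's own, but the gains need not carry over in size.

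A reader might infer that omitting size undercuts the planned power or makes the inference invalid. The documents support neither. The stated 80% is reproduced by a model without size, so the trial keeps its design power and only a possible improvement is forgone. The standard error is wrong only in the conservative direction, so the calculation shows no inflation of type I error.

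**Conclusion.** The point holds as a minor matter of efficiency. The primary estimate, as stated, leaves out the factor used to restrict the randomisation, and because the PICU effect is random this can cost some precision. With size out, the model standard error is 0 to 5% too large and type I error lies between 5.0% and 4.0%. Putting size in changes power by −0.1 point if size is unrelated to duration, and by about +1, +2.7 or +5.5 points if it explains 25%, 50% or 75% of between-PICU variance. The ceiling is about +10.6 points, if it explains all of it.

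These figures rest on an assumed share, on 17 equal-sized sites at ICC 0.005, and on the continuous-outcome approximation. It would go too far to say that leaving size out necessarily loses power: any gain depends on an association that the documents do not report.

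**What to change.** Prespecify the large/small stratum used in the randomisation (2017 PICANet volume) as a fixed covariate in the primary Cox frailty model and in the secondary mixed models. State the primary hazard ratio as adjusted for cluster, calendar time and size stratum. At the site with two PICUs, which are analysed as separate clusters, give both the class under which the site was randomised. If the analysis plan leaves size out on purpose, it should say why.

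The cost is one line of text and one degree of freedom. The classification already exists for every site, so no new data are needed. The change should be made before the outcome data are analysed.

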#### ​Internal pilot study

An internal pilot in the first four sites randomised to the intervention will evaluate and report progress during the period from randomisation to training, during training and in the 8-week period after implementing the intervention. Specifically, the following criteria will be monitored:

Actual patient numbers/month of eligible children against predictions.Feasibility of data collection procedures.Percentage of parents opting out from allowing collection of their child’s data.Delivery of training (target >80% of staff/unit trained by the end of the pilot period).Adherence to intervention components (target >75% by the end of the pilot period).

We will address criteria not achieved in pilot sites through offering support and further training as required. The pilot report will be shared with all sites. The report will inform any actions required in trial management and training to address the above criteria for all sites.

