#### ​Design

The stepped wedge design involves sequential randomised rollout of the intervention over 4-week time periods (see figure 1). Randomisation will be conducted at the hospital site (cluster) level. In general, there is one PICU per site. In one site, there will be two PICUs participating. The site will be treated as one cluster for the purpose of randomisation, and the pair will be randomised to cross from control to intervention together to avoid intervention contamination within the site. In the analysis, we will treat these two PICUs as two separate clusters. This trial requires that all participating PICUs begin the control phase of the trial when the data collection period begins. There will be an initial 8-week period of baseline data collection during which the PICU will not be exposed to the intervention. Subsequently, every 4 weeks, one site will be randomly selected to transition to the intervention and start an 8-week training period during which the intervention will be rolled out. The PICU can neither be assumed to be exposed or not exposed during training so in these 8-week periods no patients will be recruited. Once a PICU crosses over to the intervention, it will remain exposed to the intervention for the remaining duration of the study. After the last PICU has crossed over and has fully transitioned to the intervention, there will be a final 8-week period during which all PICUs will be fully exposed.

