### Intervention

Sedation and ventilator weaning in standard care will follow current best practice; this is currently non-protocol-based and medically driven. Assessment and management of sedation and ventilator weaning will be according to usual practice. Sedation levels will be assessed and recorded with a validated sedation tool, and ventilator weaning will involve a slow reduction in ventilator support until low levels are achieved consistent with readiness for extubation.

The SANDWICH intervention comprises four components:

Greater interprofessional collaboration at ward rounds including review of COMFORT scores, sedative regimen and setting targets; and ventilation and setting ventilation goals.Sedation measurement using the COMFORT tool.Regular daily assessment of criteria for readiness to perform an SBT by bedside nursing staff.An SBT and if no distress, a discussion about the decision to extubate.

The intervention training will be delivered at sites by an implementation manager who will train the trainers (local champions, principal investigators and study-specific research nurses). Training will include an online course and face-to-face instruction. A full description of the intervention was available in the study-specific training manual that was only provided to PICUs during and after the training period to avoid influencing practice during the control phase. However, at the time of publication, we are now able to release full details of the intervention, which can be found at http://www.qub.ac.uk/sites/sandwich.

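### The internal pilot report, with its training and adherence content, goes to all sites without exempting those still in the control phase, which opens an avoidable route for contamination

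*Protocol article*

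**What the plan says.** Protocol article, Internal pilot study: "An internal pilot in the first four sites randomised to the intervention will evaluate and report progress" from randomisation, through training, and "in the 8-week period after implementing the intervention". Five criteria are monitored: eligible patient numbers, feasibility of data collection, the parental opt-out percentage, training delivery (target above 80% of staff per unit) and adherence to the intervention components (target above 75%). Then: "The pilot report will be shared with all sites". And: "The report will inform any actions required in trial management and training to address the above criteria for all sites". The section names no exception for sites that have not yet crossed over, no limit on content and no circulation date.

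Protocol article, Intervention: the full description sits in a training manual that was "only provided to PICUs during and after the training period to avoid influencing practice during the control phase".

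Protocol article, Design: after an 8-week baseline, "every 4 weeks, one site will be randomly selected to transition to the intervention and start an 8-week training period". There are 18 PICUs; one site has two, and they cross together.

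**The concern.** The protocol treats influence on control-phase practice as a real threat: it holds back the manual, moves the paired PICUs together, and censors children when their unit enters transition. The circulation rule for the pilot report follows a different principle. It sends every site material on how well the first four sites trained their staff and carried out the components, and that material is meant to drive training. A site in the control phase has no use for it until its own training begins.

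The timing matters because the sites still in control after the report appears are the concurrent comparators for the units already exposed. In a time-adjusted stepped wedge analysis those late control periods carry much of the information. If some of them begin to screen for readiness or to test spontaneous breathing earlier than they otherwise would, the contrast shrinks and the primary HR moves towards 1. The planned Cox model, with a PICU frailty and calendar time, has no term that would restore the loss.

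**Working it through.** **1. Calendar (Design section).** 18 PICUs with one pair give 17 sites. Site k starts training at week 8 + 4(k − 1) and trains for 8 weeks. Site 17 starts at week 72 and finishes at week 80; the final 8 weeks end the trial at week 88, that is 22 four-week periods or about 20 months, as stated.

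**2. Reproduce the plan's figures (Sample size section).** Each site recruits in 22 − 2 = 20 periods, so N = 17 × 20 × 28 = 9520, as stated. Site k has k + 1 control periods; their sum over k = 1 to 17 is 153 + 17 = 170, which leaves 340 − 170 = 170 intervention periods.

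For power I used generalised least squares on site-period means with fixed period effects, a random site intercept and the training periods left out:
- between-site variance: 0.005 × 9.6² = 0.461
- variance of a period mean within site: 0.995 × 9.6² / 28 = 3.275
- resulting SE of the effect: 0.356 day
- power = Φ(1/0.356 − 1.960) = 80.2% (two-sided 5% assumed), against about 80% stated

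**3. Earliest date of the report.** The fourth site starts training at week 20, finishes at week 28, and its 8-week post-implementation window closes at week 36.

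| Report circulated | Intervention | Training | Still in control | Control site-periods after it |
|---|---|---|---|---|
| Week 36 | 6 | 2 | 9 | 45 of 170 |
| Week 40 | 7 | 2 | 8 | 36 of 170 |
| Week 44 | 8 | 2 | 7 | 28 of 170 |

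At week 36 site k (k = 9 to 17) has k − 8 control periods left: 1 + 2 + … + 9 = 45. At week 44 it is 1 + 2 + … + 7 = 28.

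**4. Illustration of the effect.** The documents give no figure for leakage. Let f be the share of the effect that reaches every control site-period after circulation. The estimate is linear in the period means, so expected difference = 1 − f × w, where w is the net weight of those late control cells (all control cells together have weight 1). The fit at f = 10% gives w = (1 − 0.9304)/0.10 = 0.70 for week 36 and (1 − 0.95)/0.10 = 0.50 for week 44. So 26% of the control cells carry about 70% of the net control weight in the first case.

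| Assumed f | From week 36: difference, power | From week 44: difference, power |
|---|---|---|
| 0% | 1.00 day, 80% | 1.00 day, 80% |
| 10% | 0.93 day, 74% | 0.95 day, 76% |
| 25% | 0.83 day, 64% | 0.88 day, 69% |
| 50% | 0.65 day, 45% | 0.75 day, 56% |

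Example: Φ(0.9304/0.3559 − 1.960) = Φ(0.654) = 74%. These are on the mean-difference scale that the plan used for its own power; the HR would be diluted in the same direction.

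**The case against.** A reader might infer that the report undoes the safeguard. The documents do not support that. What is held back is the full description in the manual, and nothing says the report reproduces any of it. Three of the five criteria do not concern the intervention, and the other two are percentages against targets. No outcome results are mentioned. An adherence percentage does not teach a unit the readiness criteria or how to run a breathing trial, and the intervention itself takes 8 weeks of online and face-to-face training. Sites also knew in general terms what was coming, since eligibility required them to agree to a protocolised weaning intervention. All of this stands, and it makes the larger leakage values above hard to believe.

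It is also tempting to say that a null result could not be told apart from contamination. That goes too far. Ventilator parameters are recorded daily in both phases, and in the control phase also 2 hours before extubation together with the COMFORT score; the process evaluation looks at context over time and across units. These could show some drift in control practice, although they would not correct the HR.

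Nine sites is a ceiling, not an expectation, because the report must be written after week 36.

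Finally, recruitment began on 5 February 2018 and this is version 5 of 12 March 2019, about week 57. On the stated calendar 13 of 17 sites had by then started training, so an edit to this version may come late. That limits what the change can achieve, not whether the rule is sound.

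What the objection does not remove is that the article states a positive rule, circulation to all sites, rather than leaving the matter open.

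**Conclusion.** The concern holds as a tension between two stated rules, not as a contradiction that cancels one of them. A report with training and adherence content goes to sites that the protocol elsewhere takes care not to influence: at most 9 of 17, and fewer with each month of delay. The route for contamination is avoidable, and it leads into the most informative control periods.

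The size is unknown and may be zero. The 10% case (0.93 day and 74% power from week 36; 0.95 day and 76% from week 44) shows only how sensitive the design is, with no margin above 80% planned. It rests on the protocol's planning values, an exchangeable correlation, and an assumed leak that is immediate and equal in all remaining control sites. It is not an estimate of what will happen.

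**What to change.** Replace the circulation sentence in the internal pilot section with a rule by phase:
- The full report goes to the Trial Management Group, the TSC, the DMC, the implementation manager and sites that have started training.
- Sites still in the control phase receive only the items on recruitment numbers, data collection and opt-outs.
- The training and adherence content reaches each site when its own training starts. The lessons are not lost, because the implementation manager delivers the training.

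If the report has already gone out, record its date, its content and which sites were then in control, so that readers can judge the exposure.

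Cost: one sentence in the protocol, two versions of one report, and later feedback to control-phase sites on part of the pilot.
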